**STATISTICAL ANALYSIS**

**Randomisation and masking**

Randomisation was stratified according to severity, gender, age (3−6 years or 7−12 years). Participants will be allocated (1:1) to the probiotics or placebo group using a concealed random allocation from a computer-generated random numbers table produced by Python (a cross-platform computer programming language). The additives used for the placebo group will have the same packaging, taste, and weight as the experimental group, except for the ingredients. All participants and doctors will be blind to the allocation of treatments.

**Sample size calculation**

The sample size will be calculated using Epitools (<https://epitools.ausvet.com.au/onemean>). The expected difference between the probiotic and placebo groups is based on a previous study on ASD, in which the standard deviation value of behaviour score was 8.32 in the ASD group^[31]^. To detect a clinically significant difference in the outcome measures with the condition of 90% power (α = 0.05; two-sided), 67 children are required for each group. Based on clinical study experience ^[40]^, we presume a drop-out rate of 19% through infection, efficacy, compliance, use of antibiotics, or other unforeseeable factors, implying a minimum of 80 children for each group.

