**Assessment of** **core symptoms**

All parents/guardians will be asked to complete an Autism Treatment Evaluation Checklist (ATEC) ^[32]^ to evaluate changes in core symptoms in Children with ASD at the time of the baseline, the third month, and the sixth month respectively. The scale consists of four subscales: speech, perception, social interaction, and behaviour. The total score is 0-179; the higher the score, the more serious the condition. The reduction rate of ATEC score before (S1) and after (S2) treatment will be used as the efficacy index (N), N = (S1- S2)/S1 × 100%. Markedly effective: NM ≥ 50%, Effective: NE: 20%−50%, Ineffective: NI < 20%. Total effective rate (NT) = (NM + NE) / total cases × 100%.

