**Primary Outcome Measure**

- 1. Efficacy evaluation
  2. Severity of disease

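### The 90% power claimed for the outcome measures rests on the SD of an unnamed behaviour score and no target difference, so it has no basis for the ATEC efficacy outcome and is not shown for CARS severity

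*Protocol*

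**What the plan says.** **Sample size calculation (Protocol).** The only variability figure is that "the standard deviation value of behaviour score was 8.32 in the ASD group". The instrument is not named. The text does not say whether 8.32 belongs to a raw score or a change, or at what time point. On the effect, it says "The expected difference between the probiotic and placebo groups is based on a previous study on ASD" and gives no number. The claim itself begins "To detect a clinically significant difference in the outcome measures with the condition of 90% power" and concludes "90% power (α = 0.05; two-sided), 67 children are required for each group". The calculator cited is "https://epitools.ausvet.com.au/onemean".

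**Primary Outcome Measure (Protocol).** Two outcomes are listed: an efficacy evaluation, and "Severity of disease". No instrument is named in that list.

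**Assessment of core symptoms (Protocol).** This section supplies the efficacy measure: "The reduction rate of ATEC score before (S1) and after (S2) treatment will be used as the efficacy index (N". N is a percentage, 100 × (S1 − S2)/S1. It is then cut at 20% and 50%, and the two upper categories are combined into a total effective rate. The ATEC total runs from 0 to 179, and "The scale consists of four subscales: speech, perception, social interaction, and behaviour".

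**Assessment of severity (Protocol).** Severity is assessed by CARS, which has 15 items and a maximum of 60 points.

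**The concern.** A power statement belongs to one endpoint on one scale: it needs the difference to be detected and the variability of that endpoint. Here the variability comes from a behaviour score, while the primary outcomes are a percentage change (or a responder rate derived from it) and a CARS rating. No section connects the two. The wording nevertheless extends the 90% to the outcome measures in general.

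The stake is interpretation. A null result would be reported as coming from a trial with 90% power, although the protocol does not establish that power for either primary outcome. This is separate from the choice of calculator: a correct two-group formula fed with 8.32 would still describe the behaviour score.

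**Working it through.** **Inputs.** From the sample size section: SD 8.32, two-sided alpha 0.05, power 90%, 67 per group, 19% drop-out, 80 per group. From the randomisation section: 1:1 allocation. Target difference: not stated.

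**1. Can 67 be reproduced?** Not from the stated inputs, because the difference is missing. Solving backwards with SD 8.32 and z-values 1.960 + 1.282 = 3.242:

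- Two-group comparison: difference = 3.242 × 8.32 × √(2/67) = 4.66 points, a standardised difference of 0.56 (4.69 points with the t distribution).
- One-sample test: difference = 3.242 × 8.32 / √67 = 3.29 points.
- Precision of a single mean, with an assumed half-width of 2 points: (1.96 × 8.32 / 2)² = 66.5, which rounds up to 67 and contains no power term.

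All three give 67. The protocol does not say which, if any, was used, so 4.66 or 4.69 points is a back-solved value and not a planned difference.

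**2. Does 8.32 carry over to the efficacy outcome?**

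- *Percent reduction.* The variance of 100 × (S1 − S2)/S1 depends on how baseline and follow-up ATEC totals vary together. It is measured in percentage points. An SD in score points cannot stand in for it.
- *Total effective rate.* The variance of a proportion in n children is p(1 − p)/n. No score SD appears in it.

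This step needs no assumption about which instrument produced 8.32.

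**3. What can 67 per group detect on the effective rate?** Let p be the control rate, q the probiotic rate and m = (p + q)/2. For 90% power (pooled variance under the null, no continuity correction), q solves

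q − p = 1.960 × √[2m(1 − m)/67] + 1.282 × √[(p(1 − p) + q(1 − q))/67].

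Example with p = 0.20 and q = 0.459: m = 0.3295. The first term is 1.960 × 0.0812 = 0.159 and the second is 1.282 × 0.0781 = 0.100. The sum is 0.259, which equals q − p.

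| Control rate (assumed) | Probiotic rate needed | Difference, percentage points |
|---|---|---|
| 10% | 32.6% | 22.6 |
| 20% | 45.9% | 25.9 |
| 30% | 57.4% | 27.4 |
| 40% | 67.5% | 27.5 |
| 50% | 76.6% | 26.6 |

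The control rates are assumptions, shown as a range because the protocol gives none.

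**4. Can the power for the ATEC total be worked out?** No. As a test, suppose all four subscales have SD 8.32 with common correlation r. The SD of the total is 8.32 × √(4 + 12r): 16.6, 22.9, 26.3 and 33.3 for r = 0, 0.3, 0.5 and 1. Take a 4.69-point effect per affected subscale and 67 per group (two-sample t-test):

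| Subscales affected | Total difference | r = 0 | r = 0.3 | r = 0.5 | r = 1 |
|---|---|---|---|---|---|
| One | 4.69 | 37% | 22% | 18% | 13% |
| Two | 9.4 | 90% | 65% | 54% | 37% |
| Four | 18.8 | >99.9% | 99.7% | 98.4% | 90% |

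One set of SD assumptions gives anything from 13% to over 99.9%, depending on a difference that the protocol does not state.

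**5. CARS.** The protocol gives neither an SD nor a target difference for CARS, so no power can be computed.

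**The case against.** The strongest defence has three parts.

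First, the instrument behind 8.32 is unnamed, and the details lie in the cited study. Reading the behaviour score as the ATEC behaviour subscale is an inference from a shared word. This stands. It cannot be said that 8.32 is wrong for CARS, or that it is a cross-sectional SD; only that no link is shown. It does not rescue the efficacy outcome, because a score-point SD from any instrument fails there.

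Second, the primary outcome list names neither ATEC nor CARS, and the primary hypothesis mentions repetitive and stereotyped behaviour, so a behaviour score is not foreign to the question. This is true. But the section on core symptoms calls the ATEC reduction the efficacy index, the section on severity uses CARS, and neither offers an alternative.

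Third, a reader might infer that power is overstated for the ATEC total, since a sum of four subscales normally varies more than one. The documents do not support this. The inference enlarges the SD while holding the difference at a back-solved 4.69 points, as if only one subscale responded. With all four responding, the same model gives 90% or more.

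A statistical analysis plan not shown here could hold a better calculation, but it would not correct the claim that the protocol makes.

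**Conclusion.** The point holds in a limited form. For the efficacy outcome as the protocol defines it, the stated 90% power has no basis; this follows from the scale of the outcome alone. For severity by CARS, 90% power is not shown to apply. For the ATEC total, neither the direction nor the size of any error can be determined without a target difference and an SD on that scale.

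A reader might also conclude that the 90% at least holds for the behaviour score. That is not supported either: without a stated difference it cannot be verified for any measure.

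The one figure that stands independently of 8.32 is the detectable difference in effective rate at 67 evaluable per group, 22.6 to 27.5 percentage points. It assumes control rates of 10% to 50% and the pooled two-proportion test. The protocol does not say that it expects an effect of that size.

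**What to change.** In the sample size section, withdraw the statement that the trial has 90% power for the outcome measures on the strength of 8.32. Keep 80 per group. Name the primary endpoint on the scale on which it will be analysed, and restate the power or the detectable difference for it at that number.

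- **If the total effective rate is primary:** state the expected control rate and the detectable difference in proportions, using the table above for 67 evaluable per group.
- **If a continuous ATEC endpoint is primary:** use the SD of that endpoint, for example a blinded pooled SD from data already collected, with an explicit target difference. A new SD without a target difference would leave the claim just as uncheckable.
- **If CARS severity stays co-listed as primary:** give its own SD and difference, or say that no power is claimed for it.

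Limiting the 90% to the behaviour score is not a remedy, for the reason given in the verdict.

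The cost is a rewritten paragraph and a short blinded calculation, with no extra patients. The drawback is that the stated figure may become less favourable.

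### Enrolling 80 children per group does not cover 19% drop-out from a required 67: about 65 would remain, and 83 would be needed

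*Protocol*

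**What the plan says.** The section Sample size calculation gives three linked figures.

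- The base number: "67 children are required for each group", for "90% power (α = 0.05; two-sided").
- The allowance for loss: "we presume a drop-out rate of 19% through infection, efficacy, compliance, use of antibiotics, or other unforeseeable factors".
- The result: "implying a minimum of 80 children for each group".

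The protocol does not show the formula that leads from 67 to 80. Allocation is 1:1 (Randomisation and masking), so the total implied is 160. The section Interim Analysis places the interim look at 40 children per group, and Data Collection & Monitoring places it at half of recruitment. Both fit a target of 80 per group, so 80 is the working enrolment figure.

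**The concern.** The passage presents 80 as the floor that still leaves 67 evaluable children per group after the expected losses. A drop-out rate is a proportion of the children who enter, so the enrolled number has to be multiplied by 0.81 to find how many remain. For 80 the result is below 67. The protocol therefore misses its own evaluable number at its own assumed drop-out rate, and the power it quotes is not quite reached. At stake are the accuracy of the enrolment target and of the claim that the design protects against a 19% loss.

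**Working it through.** **Inputs, all from Sample size calculation:** required evaluable number n = 67 per group; drop-out d = 0.19; stated enrolment 80 per group; power 90% at two-sided α = 0.05.

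**1. Reproducing the stated 80.** Adding 19% of the required number gives n × (1 + d) = 67 × 1.19 = 79.73, which rounds up to 80. Of the two usual ways of inflating for drop-out, only this one returns the protocol's figure.

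**2. Enrolment that leaves 67.** If N children enrol and a fraction d is lost, N × (1 − d) must be at least n. So N = n/(1 − d) = 67/0.81 = 82.72, rounded up to 83. Check: 83 × 0.81 = 67.2.

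**3. What 80 leaves.** 80 × 0.81 = 64.8, about 65 per group and 2 short of 67. The largest loss that 80 can absorb is 1 − 67/80 = 0.1625, or 16.25%.

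**4. Size in children.** 83 − 80 = 3 per group; 166 − 160 = 6 in total.

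**5. Size in power.** The protocol states no target difference, so the 67 cannot be rebuilt. The loss can still be found by taking as given that 67 per group yields exactly 90%. Under the normal approximation,

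power(m) = Φ(√(m/67) × (1.960 + 1.282) − 1.960),

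where m is the evaluable number per group. The standard deviation and the target difference cancel, so the result is the same for a one-sample and a two-sample formula.

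| Evaluable per group | Power |
|---|---|
| 67 | 90.0% |
| 65 | 89.1% |
| 64.8 | 89.0% |
| 64 | 88.7% |

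The cost at the planned drop-out rate is about one percentage point.

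**6. Chance of keeping 67.** If each child independently has a 19% chance of dropping out (an assumption made here), the probability that a given group keeps at least 67 children is 0.32 with 80 enrolled and 0.59 with 83.

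**The case against.** Four points can be made for leaving the text alone.

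- **The effect is slight.** Two evaluable children per group and about one point of power would change no estimate, test or conclusion. This stands, and it limits the weight of the finding. It does not make the figure correct.
- **The formula is inferred.** The protocol never writes 67 × 1.19, and 80 could be a convenient round number. This also stands. The conclusion does not depend on it, because 80 fails the check in step 3 however it was reached.
- **The final analysis is by intention to treat.** If every child who left still provided outcome data, all 80 would count. But the sample size section itself treats drop-outs as children to be made up for; otherwise there would be no reason to go beyond 67. The exit criteria also include children who cannot complete the compulsory scales, which is a direct loss of outcome data. This objection does not rescue the figure.
- **The 67 cannot be verified.** With no target difference stated, correcting the last step to 83 could suggest a precision that the first step lacks. This is a fair caution: 83 is right only on the condition that 67 is right.

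**Conclusion.** The point holds. Taking 67 and 19% as the protocol gives them, the minimum enrolment is 83 per group, not 80. At 19% drop-out, 80 per group leaves about 65 evaluable children and covers a loss of only about 16%. Power falls from 90% to about 89%, assuming that 67 per group gives exactly 90%. This is a definite error in a headline figure with a small practical consequence. It does not threaten the validity of the trial. That the 19% was added to 67 is the likeliest explanation but remains an inference.

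**What to change.** Correct the last sentence of Sample size calculation in one of two ways.

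- **Keep 80 per group.** State that 80 allows for about 16% drop-out, and that at 19% about 65 per group would remain evaluable, with power about one percentage point below 90%. This costs one sentence and no extra recruitment, and it is sufficient.
- **Keep the 19% allowance.** Restate the minimum as 83 per group, showing 67/(1 − 0.19) = 82.7. This costs six more children in total. The interim trigger of 40 per group would then need to be aligned with half of recruitment, since half of 83 is 41.5.

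Whichever is chosen, print the inflation formula so that a reader can check the step.

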**Data Monitoring and Interim Analysis**

**DATA COLLECTION & MONITORING**

Data collection and monitoring of study centre will be done by the centre co-ordinators. Data will be passed on to the Department of Medical Documentation of the Third Affiliated Hospital of Zhengzhou University, China, for analysis. Safety and interim analyses will be done when half of the patients are recruited, and these will be reviewed by the Safety and Data Monitoring Committee.

Centre co-ordinators will meet every month to maintain the consistency of procedures when documenting site visits, and sample chart reviews by centre co-ordinators will be reviewed by the principal investigator.

**INTERIM ANALYSIS**

Safety analysis will be executed to compare the adverse effects in the probiotics and control groups if there erupt large batch of adverse gastrointestinal reactions or other allergic symptoms within two weeks after taking probiotics.

Interim analysis will be done when 40 of the patients in each group have been recruited and 3 months of data are available.

If the trial is stopped prematurely, the patients already included in the study will be followed up as scheduled by this study protocol.

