**Synopsis**

This randomized, controlled study aims to figure out the role of probiotics in core symptoms and severity in children with autism. Secondary objectives are to determine whether probiotics regulate gastrointestinal disorders and sleep disturbances which often troubled children with autism, as well as its effect on blood and fecal metabolites, intestinal flora, and immune system.

Patients aged 3 to 12 years will be eligible if they are defined as having ASD by two child psychologists using DSM-5, but if they meet one of the following exclusion criteria they will not be allowed to take part: (1) they have taken antibiotics or antifungal drugs within three months; (2) they have a special diet, such as a gluten free diet, a casein diet, or a special carbohydrate diet; (3) they have taken prebiotics, probiotics, or antioxidants within the previous three months; (4) they have had diarrhoea, fever, or other clear inflammatory reactions within the past week; (5) they have neurological symptoms such as epilepsy; (6) they have Crohn’s disease, inflammatory bowel disease, food intolerance, or any other gastrointestinal diseases; (7) they have a liver disease; (8) they have type 1 diabetes mellitus; (9) they have a confirmed diagnosis of Rett syndrome or any other genetic metabolic disease.

All participants will be provided written informed consent before they approved to take the probiotics as required. The patients will be divided into treatment group and control group according to their severity, gender and age randomly. The treatment group will receive probiotics treatment for three months before three months withdrawal. The control group will be given the same amount of maltodextrin. The treatment and nursing of the two groups are in accordance with the same standards.

Therapeutic effect evaluation will be done at 1, 2, 3, 6 and 12 months after taking probiotics. 3, 6, 12, and 18 months by the ATEC, CSHQ, Birstol and other scales. The primary outcome was whether probiotics could alleviate poor language and cognition, narrow interest ranges, and gastrointestinal and sleep disorders in children with autism.

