**Hypotheses**

Primary: Probiotic supplements could relieve the core symptoms of autism，such as the narrow range of interests or activities and repetitive and stereotypical behavior.

Secondary(a): Probiotics can help balance gastrointestinal disorders in children with autism, such as constipation and diarrhea.

Secondary(b): Metabolites from the gut flora help improve sleep disorders.

Secondary(c): The metabolites of intestinal flora contribute to the improvement of immunity.

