**Study design**

Experimental group: Oral probiotic mixture of 5 billion CFU/5g, twice a day in the morning and once in the evening respectively, for 3 months.

Control group: The same amount of maltodextrin, treatment course and usage were the same as experimental group.

Both groups were given the same nursing and diagnosis and treatment plan.

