**STUDY PROCEDURES**

Before the trial, all the children will be evaluated carefully, and the research topic will be explained to the parents of the Children with ASD who meet the study’s selection criteria. If they are then willing to participate in the trial, they will receive the supplements free of charge for three months and carry out the relevant inspections and tests. They will sign an informed consent agreement. They will be able to consult with the doctors if they have any questions when they are administering the supplements, but they must follow the requirements of the agreement. If they are not willing to continue the study for some reason, they can withdraw. All the potential side effects will be monitored and all the participants will be recalled at 3 months after intervention for the systematic physical examination and liver as well as kidney function analysis. The potential costs will be covered by indemnity for negligent harm. The participants will be asked to provide a one tube faeces sample 0, 1, 2, and 3 months after taking the supplements, and a tube of blood with heparin anticoagulation at 0 and 3 months. To guarantee quality all samples must be transported within 12 hours at low temperatures or they will be rejected. Other than the samples used for flow cytometry detection, which has to be completed within 12 hours, all samples will be aliquots and frozen in a freezer at -80℃.

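### The for-cause safety trigger covers only the first two weeks of a three-month course, so a later cluster of reactions cannot call the between-arm comparison

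*Protocol*

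**What the plan says.** Protocol, Interim Analysis: a safety analysis will "compare the adverse effects in the probiotics and control groups if there erupt large batch of adverse gastrointestinal reactions" or other allergic symptoms arise "within two weeks after taking probiotics". No other sentence in the protocol names a comparison of adverse effects between the two arms.

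The neighbouring text gives the context:

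- **Study design:** dosing is "twice a day in the morning and once in the evening respectively, for 3 months".
- **Synopsis:** "Therapeutic effect evaluation will be done at 1, 2, 3, 6 and 12 months after taking probiotics". The Follow-up section gives the same visits, with blinded scale assessments.
- **Study Procedures:** "All the potential side effects will be monitored", with no method stated. Families are told that "They will be able to consult with the doctors if they have any questions when they are administering the supplements". All participants are recalled at 3 months for a physical examination and liver and kidney tests.
- **Data Monitoring and Interim Analysis:** a safety analysis takes place at half recruitment, without any condition, and goes to the Safety and Data Monitoring Committee. Arms and endpoints are not named.
- **Interim Analysis:** "Interim analysis will be done when 40 of the patients in each group have been recruited and 3 months of data are available".
- **Final Analysis:** the list includes a description of every observed variable. It compares the groups for comparability and evaluates efficacy; safety has no item of its own.

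**The concern.** A for-cause trigger is useful when it can fire at any point where harm could emerge. This one closes on day 14 of a course about six times as long, and before the month-1 visit, which is the first scheduled contact after baseline. Inside the window, detection rests on monitoring of unstated method and on families contacting the doctors. After the window the trigger no longer operates, however many reactions occur. The 3-month examination and laboratory results fall outside it by timing alone.

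At stake is whether harm that builds up later in the course, in children aged 3 to 12, would prompt an unscheduled look by arm. A second issue is that the one comparison named by arm depends on what the data happen to show, so a reader of the final report could not take its presence or absence at face value. The primary efficacy result is not affected.

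**Working it through.** The protocol gives no figure of its own on this point, so there is none to reproduce. The check compares durations and sets the sections side by side.

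**Inputs.** Trigger window: two weeks = 14 days (Interim Analysis). Course: 3 months, taken as 90 days, range 84 to 92 by convention (Study design). First visit: month 1, about day 30 (Synopsis, Follow-up). Sample: 80 per group, 160 in all, with 19% drop-out allowed for (Sample size calculation). Interim: 40 per group.

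**From when do the two weeks run?** The Synopsis counts its visits with the same phrase, after taking probiotics, and Study Procedures counts stool samples from month 0 on that footing. The natural reading is two weeks from the first dose.

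**Share of the course covered.**
- 14/90 = 15.6% (14/84 = 16.7%; 14/92 = 15.2%).
- Dosing days outside the window: 90 − 14 = 76 (70 to 78 across the range).
- Day 14 falls before month 1.

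**Share of first reactions covered.** The protocol gives no onset times. If the onset hazard were constant and the 90-day incidence p were 5% to 30% (both assumptions), the hazard is h = −ln(1 − p)/90 and the share in the window is (1 − exp(−14h))/p. This gives 15.9% at p = 5% and 18.0% at p = 30%. Early-clustered onset would raise it.

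**What else would catch a later reaction?**

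| Kind of harm | Two-week trigger | Half-recruitment safety analysis | End of trial |
|---|---|---|---|
| Gastrointestinal, after day 14 | No | Yes, children accrued by then | Secondary outcome, blinded, five visits; also described |
| Allergic or other, after day 14 | No | Yes, children accrued by then | Described; no comparison by arm stated |
| 3-month examination, liver, kidney | No | Where available by then | Described; no comparison by arm stated |

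The gap is in the last two rows, and chiefly in the 160 − 2 × 40 = 80 children recruited after the interim look.

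**What the later children add.** If no child on probiotics has a given reaction, the one-sided 95% upper limit for its true rate is 1 − 0.05^(1/n):
- n = 40 (interim): 7.2%
- n = 65 (80 × 0.81 = 64.8, after drop-out): 4.5%
- n = 80 (all randomised to probiotics): 3.7%

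Using all the children therefore roughly halves the rate of harm that cannot be excluded, with data that will exist in any case.

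**The case against.** The strongest reply is that the sentence stands under Interim Analysis, beside a safety analysis already scheduled at half recruitment. Read together, there is one scheduled look plus an extra one if an early cluster appears. A for-cause look is conditional by nature, and a committee reviewing safety in a two-arm trial would plausibly see it by arm. Final adverse-event tables and the exact count that makes a cluster are commonly left to the analysis plan, which is not shown. Nearly all of this stands: their absence is no fault in the protocol, and the sentence is best read as a for-cause trigger. What it leaves untouched is the stated limit of two weeks.

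Three stronger readings are tempting and unsupported.

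- A reader might infer that no other safety analysis is planned. The half-recruitment analysis and the description of all observed variables rule that out.
- A reader might infer that only 14 days of data would be compared. The text sets the window for the trigger and does not restrict the comparison.
- A reader might try to state how likely the alert is to miss real harm. The protocol gives no rates, onset pattern or threshold. With 80 per arm, assumed incidences of 10% and 30% and even onset, the chance of an alert inside 14 days is 13% at a threshold of 8 children, 56% at 5 and 88% at 3. With half of all events in the first two weeks it is 99% at a threshold of 8. Nothing in the document chooses among these, so no such figure should carry the claim.

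Gastrointestinal harm, the one adverse effect the protocol anticipates, is also the least exposed. The hypothesis that "Probiotics can help balance gastrointestinal disorders in children with autism, such as constipation and diarrhea" makes it a secondary outcome, and its analysis would show a difference in either direction.

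**Conclusion.** The point holds as a minor one. The for-cause trigger is set too narrowly: it covers about 16% of the dosing period, and a cluster that begins in the remaining 76 or so days cannot call the comparison. The practical exposure is confined mainly to allergic and other reported side effects and to the 3-month examination, liver and kidney results, and is greatest in the half of the sample recruited after the interim look. The conclusion rests on a 90-day course and on counting the two weeks from the first dose; it needs no assumed event rates. An analysis plan that is not shown may already provide unconditional tables by arm. The protocol's conditional sentence would then sit awkwardly beside it and would still be worth amending.

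**What to change.** Amend the Interim Analysis section in two respects.

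1. Replace the two-week limit: *a cluster of gastrointestinal, allergic or other adverse reactions at any time during the 3-month treatment period will prompt an unscheduled review by the Safety and Data Monitoring Committee.*
2. Add: *whether or not such a review takes place, adverse effects and the 3-month examination, liver and kidney results will be summarised by arm for all randomised children, as a difference with 95% CI.*

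The cost is two sentences and one or two tables from data already collected; no visits, staff or samples are added. The downside is that a chance cluster may occasionally prompt a committee review, somewhat more often than with a two-week window.
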